#### Phase III component

The primary endpoint of the phase III component is OS in all enrolled patients. OS is defined as the time interval between registration and death from any cause, and data are censored on the last day the patient is alive. The secondary endpoints include progression-free survival, local progression-free survival, rectal resection-free survival, colostomy-free survival, the proportion of patients with cCR at the final response evaluation (by central review), the proportion of patients with cCR/near CR at the final response evaluation (by central review), the proportion of patients who do not undergo rectal resection, adverse events, incidence of surgical morbidities, concordance of response evaluation between the central review and the institutional in-house review, the proportion of patients with R0 resection among those who undergo radical surgery, the proportion of patients with tumour progression among those who undergo W&W, defecation and anal function (Wexner and Low Anterior Resection Syndrome scores^21,22^), urinary outcomes (International Prostate Symptom score^23^), and sexual function in male patients (score on the five-item version of the International Index of Erectile Function^24^). Progression-free survival is defined as the time interval between registration and disease progression (including events after cCR/near CR or radical surgery) or death from any cause. The data are censored on the last day the patient is alive without any evidence of disease progression. Wexner and International Prostate Symptom scores and the score on the five-item version of the International Index of Erectile Function^24^ are evaluated before treatment and at 1 year and 5 years after registration.

### Participant timeline and follow-up schedule

Written informed consent will be obtained before registration from all patients who meet the inclusion criteria and do not fulfil any of the exclusion criteria. All study participants will be followed up for at least 5 years after enrolment. The primary endpoint will be analysed at 6 months after completion of patient enrolment in the phase II component and 5 years after completion of patient enrolment in the phase III component. Patients who are judged to have cCR or near CR at the final response evaluation and undergo W&W will be evaluated by chest CT, enhanced abdominal and pelvic CT and MRI, rectal examination, lower gastrointestinal endoscopy, and measurement of tumour markers (carcinoembryonic antigen and carbohydrate antigen 19-9) at 12-week intervals for 2 years after the final response evaluation and at 24-week intervals for 3 years thereafter. Patients who undergo radical surgery or local resection will be assessed by chest CT, enhanced abdominal and pelvic CT, and measurement of carcinoembryonic antigen and carbohydrate antigen 19-9 levels at 12-week intervals for 2 years after the final response evaluation and at 24-week intervals for 3 years thereafter. Colostomy status and anal function (preserved or non-preserved) will be evaluated at 6-month intervals for 3 years after initiation of irradiation and at 12-month intervals thereafter.

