#### Evaluation of response after consolidation chemotherapy to determine whether the subsequent treatment strategy should be a watch-and-wait strategy, radical surgery, or local resection

After consolidation chemotherapy, the second response evaluation is performed on days 28–43, with day 0 being the last day of the fourth course of CAPOX. For patients who have not completed consolidation chemotherapy, the second response evaluation is performed on days 28–43, with the final day of consolidation chemotherapy being day 0.

If the second response evaluation indicates cCR, W&W is chosen. However, if the response is deemed to be incomplete, radical surgery is performed. Subsequent response evaluations are scheduled to be conducted no more than twice every 8 weeks for patients achieving near CR. According to the results of the response evaluation, one of the three types of treatment, namely W&W, local resection, or radical surgery, is selected. If distant metastasis occurs, the protocol treatment is terminated, and post-study treatment is not regulated.

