#### Watch-and-wait strategy: non-operative follow-up

W&W is initiated for patients who achieve cCR at any of the second to fourth response evaluations or near CR at the fourth response evaluation (regarded as the final response evaluation) and express willingness to undergo W&W after consulting with a primary physician. W&W should be carried out until disease progression or relapse is detected. After the final response evaluation, follow-up should be conducted at 12-week intervals for 2 years and at 24-week intervals for 3 years thereafter. In the event of recurrence or progression of the primary tumour or involvement of regional lymph nodes, radical surgery is recommended as off-protocol treatment.

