### Outcomes

#### Phase II component

The primary endpoint of the phase II component is the proportion of patients with cCR at the final response evaluation (as assessed by central review to enhance the robustness of the final assessment).

The secondary endpoints in phase II are the proportion of patients with a clinical/near CR at the final response evaluation (by central review), the proportion of patients who do not undergo resection of the rectum, adverse events, the incidence of surgical morbidities, and the concordance of response evaluation between the central review and the institutional in-house review.

The final response evaluation is the point when a patient achieves cCR or the fourth response evaluation, whichever is earliest. The proportions of patients with cCR or cCR/near CR are defined according to the MSKCC criteria and include all eligible patients. The proportion of patients who do not undergo rectal resection is defined as the proportion treated with W&W or local resection and includes all eligible patients. Adverse events associated with preoperative CRT and consolidation chemotherapy are assessed in accordance with the Common Terminology Criteria for Adverse Events (CTCAE) version 5.0. Surgical morbidities are evaluated according to CTCAE version 5.0 and the Clavien–Dindo classification^20^. Concordance of response evaluation between the central review and the institutional in-house review is calculated.

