Regarding the interval between completion of TNT and response evaluation, the pCR rate in the Lyon R90-01 trial was higher in the group with a 6–8-week interval between preoperative irradiation and surgery than in the group with a 2-week interval (26 *versus* 10.3 per cent respectively)^27^. In the GRECCAR 6 trial, however, there was no significant difference in the pCR rate according to whether nCRT was followed by surgery at 7 or 11 weeks^28^. Furthermore, previous studies of the efficacy of rectum-preserving therapy have typically performed response evaluations at 12–38 weeks after initiation of treatment, whereas studies that have used the cCR rate as the endpoint have generally performed response evaluations at 24 weeks after initiation of treatment^12^. In the present study, the second response evaluation, which offers the first opportunity to assess cCR, near CR, or incomplete response according to the MSKCC criteria, will be performed 24–26 weeks after initiation of treatment. The third and fourth response evaluations will be performed 32 and 40 weeks after initiation of treatment. Therefore, it can be assumed that the effect of TNT will be adequately observed.

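### The phase II primary analysis is set at 6 months after the last phase II enrolment, but the endpoint can take about 40 weeks to settle, so late-enrolled patients still at near CR would be analysed too early and the cCR rate understated

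*Protocol article*

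**What the plan says.** - **Analysis date** (*Participant timeline and follow-up schedule*): "The primary endpoint will be analysed at 6 months after completion of patient enrolment in the phase II component".
- **Endpoint** (*Outcomes, Phase II component*): "the proportion of patients with cCR at the final response evaluation (as assessed by central review", with central review as the deciding assessment.
- **When the endpoint is reached** (same section): "The final response evaluation is the point when a patient achieves cCR or the fourth response evaluation, whichever is earliest".
- **Denominator** (same section): "The proportions of patients with cCR or cCR/near CR are defined according to the MSKCC criteria and include all eligible patients".
- **Who is evaluated again** (section on response evaluation after consolidation chemotherapy): "Subsequent response evaluations are scheduled to be conducted no more than twice every 8 weeks for patients achieving near CR". The watch-and-wait section accepts "patients who achieve cCR at any of the second to fourth response evaluations", so late cCRs count.
- **Calendar** (*Discussion*): the second evaluation, the first chance to record cCR, "will be performed 24–26 weeks after initiation of treatment". For the others: "The third and fourth response evaluations will be performed 32 and 40 weeks after initiation of treatment".

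The article gives no rule for a patient whose final evaluation is still pending at 6 months.

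**The concern.** The analysis date and the endpoint definition cannot both be followed. Six months after the last phase II enrolment, the last patients have at best just had their second evaluation. Any of them at near CR then has up to two evaluations to come, and either could turn the patient into a cCR.

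This matters because the phase II test rests on this one proportion in about 40 patients. Counting pending patients as non-cCR understates the rate and costs power. Leaving them out contradicts the stated denominator and biases the rate in a direction that depends on how many of them would have converted. The Discussion defends the evaluation timetable as long enough to see the effect of treatment; a 6-month cut removes that for the last part of the cohort.

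**Working it through.** **1. The plan's own sample size.** Inputs from *Sample size and statistical methods*: threshold 20%, expected 40%, one-sided α 5%, power 80%, 38 patients required, 40 planned. The article names no test; I assume an exact binomial test, which requires at least 13 cCRs at either size.

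| n | Success if | α at 20% | Power at 40% |
|---|---|---|---|
| 37 | ≥ 13 | 0.023 | 0.778 |
| 38 | ≥ 13 | 0.029 | 0.814 |
| 40 | ≥ 13 | 0.043 | 0.871 |

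The figure of 38 is reproduced: from 38 to 42 the power stays at or above 0.80. (35 and 36 also reach 0.80, but 37 does not.)

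**2. Calendar from the Discussion.** 6 months = 365.25 / 2 / 7 = 26.1 weeks. For the last-enrolled patient, if treatment starts at once:
- second evaluation at 24–26 weeks: just inside the cut;
- third at 32 weeks: 32 − 26.1 = 5.9 weeks after the cut;
- fourth at 40 weeks: 40 − 26.1 = 13.9 weeks after the cut.

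**3. Calendar from the treatment windows in *Interventions*.** I assume 28 fractions at five per week, with the last on day 37. Add 21–35 days to the start of CAPOX, 76–83 days for four cycles (63 days plus 13 or 20, depending on which day counts as the last), and 28–43 days to the evaluation:
- second evaluation: 37 + 21 + 76 + 28 = day 162 (23.1 weeks) to 37 + 35 + 83 + 43 = day 198 (28.3 weeks);
- fourth evaluation, 16 weeks later: 39.1 to 44.3 weeks.

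So even the second evaluation can fall after the cut.

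**4. Patients affected.** 105 patients in 3.5 years is 30 per year, or 30 / 52.18 = 0.575 per week (uniform accrual assumed).
- Too late for the third evaluation: 5.9 × 0.575 = 3.4.
- Too late for the fourth: 13.9 × 0.575 = 8.0, or 20% of 40.
- If the evaluations fall 4 weeks later (start delay or longer windows; assumed): 9.9 × 0.575 = 5.7 and 17.9 × 0.575 = 10.3.

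**5. Missed cCRs and power.** Let f be the share of eventual cCRs first seen at the third or fourth evaluation, split evenly between the two. The documents do not give f, so I take 20% and 50%. With a true rate of 40%, the chance of first reaching cCR at each late evaluation is s = 0.40 × f / 2, that is 0.04 or 0.10. Pending patients stay in the denominator as non-cCR:

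missed = s × (number short of third + number short of fourth)

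observed rate = 0.40 − missed / n

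| Timing | f | Missed cCRs | Observed rate, n = 40 | Power, n = 40 | Power, n = 38 |
|---|---|---|---|---|---|
| Endpoint complete | any | 0 | 40.0% | 0.87 | 0.81 |
| Discussion schedule | 20% | 0.04 × 11.4 = 0.46 | 38.9% | 0.84 | 0.77 |
| Discussion schedule | 50% | 0.10 × 11.4 = 1.14 | 37.2% | 0.78 | 0.70 |
| 4 weeks later | 20% | 0.04 × 16.0 = 0.64 | 38.4% | 0.82 | 0.75 |
| 4 weeks later | 50% | 0.10 × 16.0 = 1.60 | 36.0% | 0.73 | 0.64 |

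A simulation with random (Poisson) accrual at the same rate gives much the same: 0.6 to 1.7 cCRs missed, and power of 0.72–0.83 for n = 40 and 0.63–0.76 for n = 38.

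**6. If pending patients were dropped instead.** Take the Discussion's expected 40% cCR and 20% near CR, leaving 40% incomplete. Among patients seen only up to the second evaluation, the rate among those settled is:
- f = 20%: 0.32 / (0.32 + 0.40) = 44%, too high;
- f = 50%: 0.20 / (0.20 + 0.40) = 33%, too low.

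**The case against.** The strongest reply accepts that the dates do not fit and disputes how much follows from it.

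- **Few patients are affected.** A cCR or an incomplete response at the second evaluation settles the endpoint, so most of the 8 to 10 late patients are already decided. This stands: the loss in the table is about 1 to 4 percentage points.
- **The downward bias depends on how pending patients are handled.** Dropping them could push the rate up, as step 6 shows. This stands as a general point, but the article puts all eligible patients in the denominator, and under that rule the bias can only be downward.
- **The size rests on assumptions.** The late-conversion share, uniform accrual and the cut-off of 13 are not in the article. With 40 eligible patients and 20% late conversion, power stays above 0.80. This stands. With the 38 patients the calculation calls for, every scenario shown falls below 0.80.
- **The second evaluation is within 6 months by the Discussion's figures.** That is true of the quoted 24–26 weeks, with no start delay. The treatment windows allow up to 28.3 weeks.
- **The consequences are limited.** Type I error is not raised, overall survival in phase III is untouched, and cCR is reported again as a phase III secondary endpoint. This stands, but the later report comes after the phase II result has been read.

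Nor does the brevity of an article explain it. The article states a definite date that conflicts with its own endpoint, and a separate analysis plan could not supply evaluations that have not yet taken place.

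**Conclusion.** The concern holds, and the timing rule is wrong as written. The contradiction follows from the article's own figures (26.1 weeks against 32 and 40 weeks) and needs no assumption. The direction follows from the stated denominator and from cCR being counted when first reached: the 6-month analysis can only understate the cCR rate.

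The size is moderate and depends on assumptions: uniform accrual, an exact test, and 20–50% of cCRs first seen after the second evaluation. On those terms about 0.5 to 1.7 cCRs are missed, and power falls from 0.87 to about 0.72–0.84 (n = 40) or from 0.81 to about 0.63–0.77 (n = 38). The harm is a higher chance of a false negative phase II result. The sample size itself needs no change.

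**What to change.** Replace the 6-month rule in *Participant timeline and follow-up schedule* with an event-based one: the phase II primary analysis takes place when every eligible phase II patient has had the final response evaluation as defined under *Outcomes*, and its central review is complete. By the treatment windows this is up to 44.3 weeks after the last patient starts treatment. With time for review, that is about 11 months after the last phase II enrolment.

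The endpoint, the sample size, the treatment and the evaluation schedule stay as they are. The cost is one sentence and a phase II result about 4 to 5 months later. The article does not say whether accrual pauses. If it continues at 2.5 patients per month (105 / 42 months), about 10 to 12 more patients are enrolled before the phase II result is known.

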### Sample size and statistical methods

Mindful that the patients in this study have a higher probability of achieving cCR owing to the regulated eligibility criteria and that some patients who would have been deemed to have cCR in previous studies might be regarded as having near CR because of the more stringent assessment by central review in the JCOG2010 study, the threshold cCR rate was set at 20 per cent in the phase II component. The expected cCR rate was then set at 40 per cent based on consensus of members of the JCOG Colorectal Cancer Study Group. With a one-sided α value of 5 per cent and 80 per cent power, the required sample size was calculated to be 38 patients. Allowing for the fact that some patients may become ineligible, the planned sample size for the phase II component of the study was finally set at 40 patients.

In JCOG0212, the 5-year OS rate for patients with cT3 N0 M0 lower RC of less than or equal to 5 cm was 95.3 per cent. Although the present study includes patients with cT2 N0 M0 disease, which has a better prognosis than cT3 N0 M0, it may be challenging to significantly improve the prognosis given the inherently favourable prognosis of this population. Therefore, the expected 5-year OS rate was set at 95 per cent, and the threshold 5-year OS rate was set at 87 per cent considering that radical surgery would not be required in about half of the patients because of TNT and W&W. Thus, the final analysis will include the phase II population. Assuming a one-sided α value of 5 per cent and 80 per cent power, the sample size needed was calculated to be 98 patients. Considering that some patients may be lost to follow-up, the planned sample size is 105 patients (phase II, 40 patients; phase III, 65 patients). The expected accrual interval is 3.5 years, and the expected follow-up duration is 5 years after completion of enrolment. All statistical analyses will be performed at the JCOG Data Centre.

### Ethics and dissemination

The study protocol was approved by the JCOG Protocol Review Committee in April 2022 and by the National Cancer Centre Hospital Certified Review Board in June 2022. The trial is registered at the Japan Registry of Clinical Trials as jRCTs031220288 (https://jrct.niph.go.jp/en-latest-detail/jRCTs031220288). All patients will receive information to assist with decision-making regarding whether to participate in the study. Consent to publication is included in the general consent form, and each participant’s data will be handled anonymously. All participant information will be stored at the JCOG Data Centre.

## Discussion

This article describes the context, methodology, and rationale of the multi-institutional, single-arm phase II/III JCOG2010 trial, which focuses on patients with cT2–3 N0 M0 RC and a tumour diameter of less than or equal to 5 cm who are likely to achieve cCR after TNT.

In this study population, radical surgery involves resection of the rectum, which results in significant deterioration of postoperative QoL in almost all patients. In JCOG0212, early dysuria was observed in 58 per cent of patients who underwent total mesorectal excision, and erectile and ejaculatory dysfunction was frequently reported in men^3^. A preoperative survey of patients with colorectal cancer found that 76 per cent hoped that surgery would be curative, 78 per cent were unwilling to receive a permanent stoma, and 74 per cent wished to avoid postoperative complications^25^. Therefore, postoperative QoL should be considered one of the essential endpoints in this population. However, potential risks associated with the TNT strategy include the increased likelihood of local recurrence, possible tumour progression requiring extended surgery, and an elevated risk of adverse events when performing definitive surgery after TNT. Therefore, it is crucial to consider the balance between efficacy and adverse events when interpreting the results of the JCOG2010 study^26^.

Regarding the interval between completion of TNT and response evaluation, the pCR rate in the Lyon R90-01 trial was higher in the group with a 6–8-week interval between preoperative irradiation and surgery than in the group with a 2-week interval (26 *versus* 10.3 per cent respectively)^27^. In the GRECCAR 6 trial, however, there was no significant difference in the pCR rate according to whether nCRT was followed by surgery at 7 or 11 weeks^28^. Furthermore, previous studies of the efficacy of rectum-preserving therapy have typically performed response evaluations at 12–38 weeks after initiation of treatment, whereas studies that have used the cCR rate as the endpoint have generally performed response evaluations at 24 weeks after initiation of treatment^12^. In the present study, the second response evaluation, which offers the first opportunity to assess cCR, near CR, or incomplete response according to the MSKCC criteria, will be performed 24–26 weeks after initiation of treatment. The third and fourth response evaluations will be performed 32 and 40 weeks after initiation of treatment. Therefore, it can be assumed that the effect of TNT will be adequately observed.

The cCR rate achieved by nCRT for cT3N0 rectal carcinoma, which is associated with feasibility of preserving the rectum, was noted to be 54.2 per cent when the two-classification system (cCR or incomplete response) was used^29^. Despite focusing on patients with cT2 N0 M0 disease, the present study considers addition of consolidation chemotherapy as TNT, which could potentially augment the cCR rate. However, the assessment criteria for treatment response entail a three-classification system (cCR, near CR, or incomplete response). It is plausible that some patients in this study who would be previously identified as having cCR could be classified as having near CR. The expected cCR and near CR rates in this study have therefore been set at 40 and 20 per cent respectively. In view of the lower probability that patients categorized as having near CR would opt for radical surgery and data from a previous report^30^, around 60 per cent of patients classified as having near CR would be expected to select W&W and 40 per cent would opt for local resection. In summary, W&W would be performed for 52 per cent of patients and local resection for 8 per cent of patients in the JCOG2010 study. Assuming that approximately 40 per cent of local resection cases and 20 per cent of W&W cases will undergo radical surgery for residual tumour or local progression, rectal preservation would ultimately be expected in 45.4 per cent of patients in the present study.

This study will include a longitudinal evaluation of anal and defecation function, urinary function, and sexual function in men. If rectal preservation by TNT and W&W is practicable, these functions may be expected to be preserved. However, there is currently no information on the degree to which TNT affects these functions, and the longitudinal analysis may provide fundamental data for clinical research and enable informed decision-making when TNT is implemented in clinical practice. An ancillary study is also planned to assess the potential value of circulating tumour DNA as a marker for therapeutic and prognostic purposes in patients with RC who are treated with TNT followed by W&W. Correlating the findings of the ancillary study with those of the present study could significantly influence clinical practice and advance the field of personalized and precision medicine.
